### Comparison of pre- and post-intervention scores

The interrupted time series analysis will estimate the impact of the intervention upon process of care and health outcome measures; however, a comparison of pre- and post-intervention scores is also necessary to estimate whether the intervention successfully changed the factors (for example, individual attitudes, social networks and team culture) in the underlying theoretical framework that it was designed to target (based on the data synthesis through multilevel modelling in TRiPLaB's development phase in each site). This 'meditational analysis' [9] is critical when evaluating the theory used to develop change interventions, as it will inform our understanding of why an intervention either works or fails to work in the ways we intended.

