**Methods:**

TRiPLaB is built around a three-stage, sequential, approach using separate, longitudinal case studies conducted with collaborating NHS organisations, TRiPLaB will select robust innovations to implement, conduct a theory-informed exploration of the local context using a variety of data collection and analytic methods, and synthesise the information collected to identify the key factors influencing the uptake and adoption of targeted innovations. This synthesis will inform the development of tailored, multifaceted, interventions designed to increase the translation of research findings into practice. Mixed research methods, including time series analysis, quasi-experimental comparison, and qualitative process evaluation, will be used to evaluate the impact of the implementation strategies deployed.

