### Evaluation phase (phase three)

Following the recommendation to conduct exploratory trials prior to embarking on more definitive randomised controlled trials [11], TRiPLaB will employ three different methods to evaluate the impact of the tailored implementation strategies delivered in each case study. The findings from these evaluation measures will inform (if worthwhile) later randomised controlled trials. The three methods to be used are: interrupted time series analysis of either tailor-made audit data or routinely collected data to estimate the impact of the intervention upon suitable process of care and outcome measures; comparison of pre- and post-intervention scores of survey-gathered measures of individual attitudes, team culture, and changing nature, composition, and size of social networks; and a qualitative process evaluation of why the intervention worked (or did not work).

Alongside these three primary evaluation methods we will also collect cost data on the resources used in the delivery of implementation approaches. The micro costs [16] associated with each strategy will be estimated alongside the extent of behavioural change achieved to arrive at summary estimates of implementation cost effectiveness [14] for each of the case studies in the programme.

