### Interrupted time series analysis

Interrupted time series designs compare multiple 'before and after' (the introduction of a change strategy) measures to detect whether an intervention has had an effect over and above any underlying trend in the data [17]. Time series analysis has been used as a technique for evaluating the effectiveness of health care interventions [18]. In the case studies, routinely collected process (health professionals' adoption of the innovation) and health outcome measures (dependent on the innovation selected) will provide the multiple time points necessary to perform a time series analysis. Time, possible seasonal trend, and possible upward trend, commonly occurring following the introduction of a new innovation [10], will be modelled into the analysis. This will be the primary outcome measure for each case study.

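### The pre-post survey comparison is called a mediational analysis, but as described it estimates only whether the targeted factors changed and does not relate that change to adoption

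*Protocol article*

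**What the plan says.** The protocol article, under 'Evaluation phase (phase three)', lists three evaluation methods. The second is a "comparison of pre- and post-intervention scores of survey-gathered measures of individual attitudes, team culture, and changing nature, composition, and size of social networks".

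Under 'Comparison of pre- and post-intervention scores' the article divides the work in two. For adoption and outcomes, "The interrupted time series analysis will estimate the impact of the intervention upon process of care and health outcome measures". For the factors in the theoretical framework, "a comparison of pre- and post-intervention scores is also necessary to estimate whether the intervention successfully changed the factors" that the intervention was designed to target. The choice of target is "based on the data synthesis through multilevel modelling in TRiPLaB's development phase in each site". The next sentence names the score comparison a 'meditational' analysis, evidently meaning mediational, and says that it "is critical when evaluating the theory used to develop change interventions, as it will inform our understanding of why an intervention either works or fails".

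Under 'Interrupted time series analysis' the stated content of the model is: "Time, possible seasonal trend, and possible upward trend, commonly occurring following the introduction of a new innovation [10], will be modelled into the analysis". This analysis is named as the primary outcome measure for each case study.

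**The concern.** A mediation claim has two links: the intervention moves the factor, and movement in the factor goes with movement in adoption. The analysis described addresses only the first.

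That first link is also weakly protected. The time series section recognises that an effect must be distinguished from an underlying trend, but it applies this only to the process and outcome series. The survey scores are described simply as before and after. General change in attitudes, the effect of being surveyed twice, or staff turnover could be read as the intervention having reached its target.

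At stake is the stated purpose of this component, which is to evaluate the theory behind the intervention. The article also says that the evaluation will inform later randomised trials if they are worthwhile, so a misread mechanism could shape their design.

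**Working it through.** **1. Is the second link supplied elsewhere in the article?**

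- *Interrupted time series analysis:* the terms named are time, season and upward trend. No framework factor is among them.
- *Exploring the local context:* the multilevel model belongs to the development phase. It identifies the level to target, before there is any change to analyse.
- *Qualitative process evaluation:* this offers interviews on perceptions plus a fidelity measure. It bears on why an intervention worked, but does not relate factor scores to adoption.

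**2. Is there a comparator for the survey scores?**

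- The abstract speaks of "Mixed research methods, including time series analysis, quasi-experimental comparison, and qualitative process evaluation". The middle item sits where the phase three section lists the pre-post comparison, and no control group is described anywhere.
- The section on the three-phase approach mentions looking at change between case studies late in the programme. It does not tie this to the survey scores or present it as a control. Each site has its own selected innovation and tailored intervention, so one site is not an obvious control for another.

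**3. What the planned analyses identify.** Let *a* be the intervention's effect on the factor, *t* the drift in the factor, *b* the slope of adoption on the factor, and *c* the adoption change that does not pass through the factor.

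- Expected pre-post factor change = *a* + *t*. One group measured twice gives the sum, not *a*.
- Expected adoption change = *c* + *b*(*a* + *t*). The time series addresses this total.
- Neither analysis estimates *b*, and having both does not recover it, because *c* is also unknown.

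**4. Illustration.** The article states no sample size, effect or error rate for this comparison, so there is no figure to reproduce. All inputs here are assumptions: 60 linked respondents, unit SD for factor change and for residual adoption change, two-sided 5% tests, 3,000 runs. The columns give the percentage of runs with a significant result.

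| Scenario | *a*, *t*, *b*, *c* | Pre-post factor change | Adoption change | Slope of adoption change on factor change |
|---|---|---|---|---|
| True mediation | 0.5, 0, 0.6, 0.2 | 96.6 | 89.4 | 99.2 |
| Factor moves, no link to adoption | 0.5, 0, 0, 0.5 | 96.5 | 97.1 | 5.3 |
| Drift only, adoption changes by another route | 0, 0.5, 0, 0.5 | 96.6 | 96.6 | 5.0 |
| No factor change, direct effect | 0, 0, 0, 0.5 | 4.3 | 97.2 | 4.3 |
| Factor effect cancelled by drift | 0.5, −0.5, 0.6, 0.5 | 5.7 | 90.8 | 99.5 |

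Approximate hand checks: for the pre-post test, 0.5 × √60 = 3.87 and 3.87 − 2.00 = 1.87, a power of about 97%. For the slope, 0.6 × √60 = 4.65 and 4.65 − 2.00 = 2.65, above 99%.

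The first three rows agree in the pre-post column by construction, since *a* + *t* = 0.5 in each. That is the point: the planned comparison sees only this sum. The last row shows that a null pre-post result can also hide a real effect on the factor.

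**5. Limit of the illustration.** Drift is the same for every unit, and in the drift row adoption changes by an unconnected route. If an outside cause *U* varied between units and moved the factor by *g* and adoption by *h* per unit of *U*, the slope would estimate *b* + *gh* Var(*U*)/Var(factor change). The linked analysis is therefore better than the unlinked one, but it does not prove mediation.

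**The case against.** The strongest reply is that this is a condensed, programme-level article. Innovations, interventions and data sources are chosen case by case, so model terms and record linkage belong in a fuller document. The component is not the primary measure, the evaluation is framed as exploratory, and the article claims only to inform understanding. Factors that did not move would be useful evidence on failure, and the interviews and fidelity measure also address why.

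Much of this stands, and it limits the point. It does not remove it: the article itself says what the mediational analysis consists of and what it is for, and the two do not match. A plan that followed the text faithfully would inherit the gap.

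Three stronger readings are tempting and are not supported:

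- **Regression to the mean.** A reader might infer that scores will rise on re-survey because the baseline survey also guides targeting. That needs selection on low baseline scores. 'Exploring the local context' selects the level most likely to respond, with a particularly influential team culture as its example. No section says low scorers are targeted, so no size can be put on such a shift.
- **No evidence at all on why.** A reader might conclude that the evaluation cannot say why an intervention worked or failed. The interviews, the fidelity measure and a null factor change all bear on that.
- **Automatic support for the theory.** A reader might infer that the theory would be declared supported whenever attitudes and adoption both rise. No such decision rule is stated.

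**Conclusion.** The point holds in a limited form. The analysis labelled mediational covers only the step from intervention to factor. It has no described comparator or trend adjustment and no stated link to adoption change. On its own it cannot separate mediation from unrelated factor change or secular drift.

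This rests on the article's wording and on the algebra above. The simulated percentages illustrate it under assumed inputs and are not estimates for this programme. The primary time series analysis is unaffected. The component should be changed because it is meant to evaluate the theory and the remedy is cheap.

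**What to change.** 1. Put a pseudonymous respondent and team code on both surveys, and analyse linked pre and post scores with the multilevel structure already planned for the development phase. Linkage does not by itself remove drift.
2. Where the routine or audit adoption data can be split by team or unit, relate each unit's adoption change to its change in the targeted factor and to its fidelity measure. Report the estimate with an interval, as an exploratory association that shared outside causes may still confound.
3. Where the data cannot be split, drop the mediational label, report the result as change in targeted factors only, and state that without a comparator the change cannot be attributed to the intervention.

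Requiring targeted factors to move more than untargeted ones is not recommended. The Background describes the influences on implementation as interconnected, so spillover could make a genuine effect look unspecific.

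Cost: a survey code and some extra modelling. With few teams the estimate in step 2 will be imprecise, and its interval should show that.

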### Qualitative process evaluation

Qualitative interviews with health professionals receiving the intervention will enable an exploration of their perceptions of what worked and what did not work in the intervention, providing insight into the 'black box' of intervention effectiveness [19]. In combination with the measure of fidelity taken during the implementation phase, these qualitative interviews comprise a process evaluation of the intervention, addressing recommendations to monitor intervention delivery and receipt by participants [11,20]. The data will be analysed using a framework approach [21]: familiarisation with the data, identification of a thematic framework, indexing, charting, and finally, mapping and interpretation with reference to the overall aim of TRiPLaB as well as the themes revealed by the data.

## Conclusion

TRiPLaB is a theory-informed, systematic, mixed methods approach to developing and evaluating tailored implementation strategies aimed at increasing the translation of research findings into clinical and service practice. TRiPLaB aims to play a part in improving the quality of health services for the people of Leeds and Bradford. By working alongside multiple healthcare organisations in a series of longitudinal case studies, the TRiPLaB programme will develop a richer understanding of key issues influencing the adoption of innovations in the NHS and the promotion of quality improvement in routine practice.
